### Evaluation indicators

2.11

#### Treatment rating scale

2.11.1

Based on the scale evaluation, PSQI, FS-14, HAS, and WAIS scales will be used to evaluate heart rate variability (HRV) of patients in each group before the first treatment, after the last treatment, and 4 weeks after the end of treatment (follow-up).

#### Rs_fMRI

2.11.2

Sleeping patients will be subjected to Rs_fMRI in the morning of the day before the start of treatment and the morning after the last treatment after completion of the 4 courses of treatment. Siemens will be first used to perform conventional MRI structural images of the brain, namely T1 and T2 scans. The test will be terminated if the brain structure was abnormal. When the standard Rs_fMRI test will be performed, the patients will be required to lie down, be quiet, close their eyes, and try not to think when scanning is being conducted. The three-dimensional “∗.DCM” file will be obtained after scanning as per the parameters design of Siemens medical system, and the original data will be saved. The image will be preprocessed by DPARSF software including conversion of “.dcm ”to“.nfTI,” Slice Timing, head Timing (Realign), Normalize, Smooth etc. The pretreatment parameter TR will be set at 2 mm; the first 10 time points will be removed; FALFF Band (Hz): 0.01 to 0.1; ReHo Ouster: 27 Voxels. Voxel Slice [3,3,3], others with default values. SPM12 software will be used for statistical analysis of the images, and Xjview software will be used for image analysis.

#### MRS detection

2.11.3

After the Rs_fMRI detection, imaging will be continued on the Siemens 3.0T scanner. The parameters will be set as SVS-SE-135 MRSI. The collection method used will be stimulated echo (STEAM). TR/TE = 2000/30 ms. Voxel size will be 20 × 20 × 20 mm^3^; the bandwidth (bandwidth) used will be 1200 Hz; acquisition duration will be 853 ms. The pixels will be obtained at 148%. The cephalopods (HFS) will be taken from the patient and the scanning location will be the hypothalamus region of the head. The results will be saved in the format of “.jpg.” The displacement value (PPM) of GABA and 5-HT will be determined and measured. The contents of GABA and 5-HT in hypothalamus will thereafter observe.

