**Methods and design::**

A single blind randomized controlled trial will be conducted. Sixty chronic insomnia volunteers and 30 healthy volunteers will be recruited for this study. Sixty insomnia volunteers will be randomly divided into a drug group and a massage group, and 30 healthy volunteers will be assigned to the healthy group. The manipulation of the treatment group will be mainly carried out through abdominal rubbing and vibration massage, once a day, 30 min/time, 5 days for a course of treatment, and a total of 4 intervention courses will be carried out. Patients in the drug group will be given orally spleen-invigorating bolus, twice a day, 1 pill in the morning and 1 pill in the evening. The course of treatment will be carried for 5 days, and a total of 4 courses of treatment will be administered.

The massage group will be compared with the healthy group and the drug group by Pittsburgh Sleep Index scale (PSQI), Hyperarousal scale (HAS), Hamilton Depression scale (HAMD), Fatigue scale-14 (FS-14), and Wechsler Adult Memory scale (WAIS) scales using to observe the sleep quality. Rs-fMRI will be used to observe various BOLD signals in the brain and compare the values of Reho, fALFF, and FC. MRS technology will be used to observe the contents of GABA and 5-HT in the hypothalamus. Additionally, the contents of cortical hormone releasing hormone (CRH), adrenocorticotropic hormone (ACTH), COR, GABA, NE, PGE2, and 5-HT in the serum will be also detected. The serum of each group will be taken for 1H nuclear magnetic resonance (^1^HNMR) metabolomics study to analyze the various common metabolites, differential metabolites, potential metabolic biomarkers, and metabolic pathways among the 3 groups. Finally, in combination with the brain functional imaging and brain spectrum, the potential mechanism of abdominal vibration and ring massage will be discussed.

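### Hypothalamic GABA is to be read from an inconsistently described, unedited 3.0T spectrum that does not reliably resolve it from creatine

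*Protocol article*

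**What the plan says.** The abstract makes brain GABA one of two spectroscopy outcomes: "MRS technology will be used to observe the contents of GABA and 5-HT in the hypothalamus". Section 2.11.3 (MRS detection) repeats this: "The contents of GABA and 5-HT in hypothalamus will thereafter observe".

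The same section specifies the acquisition in some detail:

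- Scanner: "After the Rs_fMRI detection, imaging will be continued on the Siemens 3.0T scanner".
- Parameter set: "The parameters will be set as SVS-SE-135 MRSI".
- Sequence and timing: "The collection method used will be stimulated echo (STEAM). TR/TE = 2000/30 ms".
- Voxel: 20 mm on each side, which is 8 mL.
- Read-out: "the bandwidth (bandwidth) used will be 1200 Hz; acquisition duration will be 853 ms".
- Target: "the scanning location will be the hypothalamus region of the head".
- Output: "The results will be saved in the format of “.jpg", with GABA and 5-HT identified and measured by their ppm shift.

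The section names no editing scheme, fitting model, baseline handling or fit-quality criterion. GABA is also measured in serum by ELISA (Section 2.11.5), and the Discussion lists it among the mediators in the mechanism hypothesis.

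**The concern.** There are two linked problems.

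First, the acquisition is described in two ways that do not fit together. The label SVS-SE-135 MRSI reads as a single-voxel spin echo at TE 135 ms, whereas the next statement gives stimulated echo at TE 30 ms. The label also joins single-voxel spectroscopy (SVS) with spectroscopic imaging (MRSI).

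Second, under either description the spectrum is unedited. Near 3.0 ppm the small GABA signal lies on top of the much larger creatine signal, and at 3.0T the two are closer together than a realistic in vivo linewidth. If the value at GABA's ppm position is taken as GABA content, it is mostly creatine plus baseline.

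What is at stake is the reading of a mechanistic result. A before-to-after change or a group difference reported as hypothalamic GABA could be a change in an overlapping metabolite or in the baseline. A real GABA change could equally be too diluted to see. The sleep scales are not affected.

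**Working it through.** **1. The plan's own figure.** Points = bandwidth × acquisition duration = 1200 Hz × 0.853 s = 1023.6. With the usual 1024 points (an assumption), 1024 / 1200 Hz = 853.3 ms, which matches the stated 853 ms. This is an ordinary single-voxel read-out. Its digital resolution is 1 / 0.853 s ≈ 1.2 Hz, so the limit on separating peaks is linewidth, not sampling.

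**2. Is either label an edited acquisition?** Spin echo at TE 135 ms: no. STEAM at TE 30 ms: no. The conclusion is therefore the same whichever description is meant.

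**3. Peak separation.** The proton frequency at 3.0T is 42.577 × 3.0 ≈ 127.7 MHz. The GABA-creatine separation near 3.0 ppm is not in the document; I assume 0.02 ppm, range 0.01-0.03.

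- 0.01 ppm: 1.3 Hz
- 0.02 ppm: 2.6 Hz
- 0.03 ppm: 3.8 Hz

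An assumed in vivo linewidth of 5 Hz or more (6-15 Hz for deep brain) exceeds all three, so the peaks merge.

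**4. GABA's share of the joint signal.** Assumed: GABA g = 1-2 mM (2 protons) and creatine c = 6-9 mM (3 protons). All formulas treat the joint peak as a single undivided signal.

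- Share = 2g / (2g + 3c)
- Change in joint signal from a true 20% GABA rise = 0.20 × share
- Apparent GABA change from a creatine change of x = x × 3c / (2g)

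| | g = 1, c = 9 | g = 2, c = 6 |
|---|---|---|
| GABA share | 2/29 = 6.9% | 4/22 = 18.2% |
| Joint signal moved by a 20% GABA rise | 1.4% | 3.6% |
| Apparent GABA change, creatine +2% | 27% | 9% |
| Apparent GABA change, creatine +5% | 68% | 23% |
| Apparent GABA change, creatine +10% | 135% | 45% |

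Put the other way, the creatine change that imitates a 20% GABA rise is 0.20 × 2g / (3c): 1.5% at g = 1, c = 9 and 4.4% at g = 2, c = 6.

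**5. Sensitivity to the concentration assumption.** Using GABA:creatine ratios instead, the creatine-to-GABA area ratio is 3 / (2 × ratio). At 1:10, 1:8 and 1:5 it is 15, 12 and 7.5, so GABA is 6%, 8% and 12% of the joint signal. A 5% creatine change then equals 75%, 60% and 38% of the GABA area. The picture is the same.

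**The case against.** The strongest objection is that step 4 books the whole of any creatine change as GABA. That is true only if one merged peak is read. GABA has other multiplets, and a basis-set fit to short-TE data estimates creatine as its own term, so the 23-68% would no longer apply. The article names no such fit, but an article may leave processing to the full protocol. This part stands. A reader might infer that GABA cannot be measured at all from this spectrum; the documents do not support that. They support a narrower statement: as described, with a ppm-position reading and image output, GABA is not reliably resolved. A fit would improve this but leave GABA weakly estimated and dependent on the creatine and baseline model.

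A second objection is that overlap common to both randomised arms mainly adds noise and dilutes an effect. A spurious massage-versus-drug difference needs creatine or baseline to change differently by arm, and nothing in the document shows that it would. This also stands, so a reader should not infer that any between-arm GABA difference would be an artefact. The point is that such a difference could not be attributed to GABA with confidence. Randomisation gives no such protection to the paired before-and-after tests in Section 2.13 or to comparisons with the healthy group.

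Third, the shifts, concentrations, linewidths and size of creatine change all come from outside the document. That is so, and ranges are shown for this reason.

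Fourth, the importance is limited. The Discussion lists GABA among mediators in the body, not specifically as a brain measurement, and it is one of many mechanistic measures. That is correct and limits the weight of the point.

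**Conclusion.** The point holds in this limited form. Section 2.11.3 contradicts itself on sequence and echo time, and neither description is an edited acquisition. Followed as written, the plan would report a poorly resolved signal as hypothalamic GABA content. This is not a complaint about missing detail, because the article itself states the sequence, the echo time and the way GABA is read.

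The size depends on assumptions. With GABA 1-2 mM and creatine 6-9 mM, GABA is about 7-18% of the joint signal, and a 5% creatine change passes for a 23-68% GABA change when creatine is not fitted separately. The 5% is illustrative; the effect scales in proportion. Nor is STEAM the only acquisition named, so the stated TE of 30 ms cannot be treated as settled until the passage is reconciled.

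The consequence is confined to one mechanistic outcome. Sample size, error rate and the sleep endpoints are untouched.

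**What to change.** 1. In Section 2.11.3, reconcile the parameter-set label with the stated sequence and echo time, so that one acquisition is described.
2. If the site can already run an edited acquisition with adequate signal in this 8 mL hypothalamic voxel, use it and report the result as GABA+, a label that concedes the edited signal is not pure GABA. The document does not show that this is feasible, so it should not be assumed.
3. Otherwise, in the abstract and Section 2.11.3, either remove hypothalamic GABA content as an MRS outcome, or label it exploratory and not reliably resolved, estimated by model fit with a fit-quality limit set in advance. A fit needs the numeric spectrum, not only an image.
4. Report the metabolites that the spectrum does resolve. Keep serum GABA (Section 2.11.5) as a separate measure, without presenting it as a substitute for brain content.

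The cost is one mechanistic outcome lost or downgraded, or a longer spectroscopy block in the existing session. The metabolites left to report may not bear directly on the mechanism hypothesis. No extra visit is needed.

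### Hypothalamic 5-HT is fixed as a 3T single-voxel MRS outcome, although under any plausible assumed level it lies at least about 10-fold below what that acquisition can detect

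*Protocol article*

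**What the plan says.** The protocol article commits to the outcome twice. The Methods part of the Abstract states: "MRS technology will be used to observe the contents of GABA and 5-HT in the hypothalamus". Section 2.11.3 (MRS detection) closes with: "The contents of GABA and 5-HT in hypothalamus will thereafter observe".

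Section 2.11.3 also fixes the acquisition:

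- Field strength: "imaging will be continued on the Siemens 3.0T scanner".
- Sequence label: "The parameters will be set as SVS-SE-135 MRSI". The next sentence names stimulated echo (STEAM) as the collection method.
- Timing: "TR/TE = 2000/30 ms".
- Volume: "Voxel size will be 20 × 20 × 20 mm^3".
- Readout: a bandwidth of 1200 Hz, and "acquisition duration will be 853 ms".

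The ppm position of each of the two metabolites is then to be read, and results are stored as .jpg pictures. No spectral editing, expected 5-HT level, detection limit or validation for 5-HT is stated.

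The only other 5-HT measurement is in serum, by ELISA (section 2.11.5). Section 2.13 gives general methods for all data: paired t tests before and after treatment, one-way ANOVA between groups, and P < .05 counted as a difference.

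**The concern.** In-vivo MRS of this kind sees metabolites that are present at roughly millimolar level. Brain 5-HT is taken to be at micromolar level or near it. If so, the obstacle is sensitivity. A fuller protocol could add peak fitting, quality thresholds or a better file format, but none of these creates a signal that is not there. The point is therefore an outcome fixed badly, not detail that a journal article leaves out.

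A number would still be produced, because something can always be read at a given ppm position. Pure noise tested at P < .05 has a 5% chance of a false difference per test. An overlapping metabolite is worse: a real change in another substance would be labelled serotonin. A null result would be equally uninformative. The Abstract says that the brain spectrum will be combined with functional imaging to discuss the mechanism, so such a value could be presented as evidence of a central serotonin effect.

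**Working it through.** **Inputs from section 2.11.3:** 3.0T; STEAM; TR 2000 ms; TE 30 ms; voxel 20 × 20 × 20 mm; bandwidth 1200 Hz; readout 853 ms.

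**Assumed inputs (not in the article):** proton MRS, since the nucleus is not named but the GABA target and short TE imply it; brain tissue 5-HT of 0.0001 to 0.01 mM; in-vivo detection limit at 3T of 0.1 to 1 mM; 1024 readout points; 128 averages per scan.

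**Step 1, the plan's own figure.** Readout time = points / bandwidth = 1024 / 1200 Hz = 0.853 s, which matches the stated 853 ms. Voxel volume = 20 × 20 × 20 = 8000 mm³ = 8 mL. This shows only that the readout is a conventional one. It says nothing by itself about whether 5-HT can be detected.

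**Step 2, the gap.** Ratio = detection limit / tissue level.

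| Assumed limit (mM) | 5-HT 0.0001 mM | 5-HT 0.001 mM | 5-HT 0.005 mM | 5-HT 0.01 mM |
|---|---|---|---|---|
| 0.1 | 1,000 | 100 | 20 | 10 |
| 0.5 | 5,000 | 500 | 100 | 50 |
| 1.0 | 10,000 | 1,000 | 200 | 100 |

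The most favourable corner is 0.1 / 0.01 = 10. The least favourable is 1 / 0.0001 = 10,000.

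**Step 3, what would reverse the conclusion.** The ratio must fall to 1. With the limit at 0.1 mM, tissue 5-HT would have to be 0.1 mM, ten times the top of the assumed range. With 5-HT at 0.01 mM, the limit would have to be 0.01 mM, a tenth of the lowest assumed limit.

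**Step 4, whether longer scanning closes the gap.** Signal-to-noise grows with the square root of the number of averages, so the scan-time factor is the ratio squared. Base scan = 128 × 2 s = 256 s = 4.3 min.

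- 10-fold gap: 10² = 100; 100 × 256 s = 25,600 s, about 7.1 hours per scan.
- 50-fold gap: 50² = 2,500; 2,500 × 256 s = 640,000 s, about 178 hours per scan.

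**Step 5, the settings set side by side.** These conflicts affect both metabolites. On the usual reading, the label in section 2.11.3 denotes a single-voxel spin-echo sequence with an echo time of 135 ms. The text beside it gives a stimulated-echo method with TE 30 ms. The label also joins a single-voxel abbreviation to one for spectroscopic imaging. A ppm position identifies a resonance and is not a concentration, and a .jpg does not preserve the spectrum for quantification.

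**The case against.** The strongest objection is that the decisive figures come from outside the article. The ratio is one assumption divided by another, no document figure enters it, and a different choice of range moves the best corner: with 0.001 to 0.01 mM and a limit of 0.3 to 1 mM, the gap would be 30- to 1,000-fold. This stands as a limit on certainty, and the claim must be conditional. It does not overturn the point, because the assumptions are declared, the wider range is the one used, and every corner of both ranges leads to the same conclusion. Matching the 853 ms readout lends it no support.

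Three stronger readings are tempting, and the article does not support them.

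- *The mechanism hypothesis loses its 5-HT evidence.* The Discussion lists 5-HT among mediators in the body and does not specify brain 5-HT. Serum 5-HT by ELISA addresses that wording, though only peripherally.
- *The plan expressly tests MRS 5-HT by ANOVA and paired t test.* Section 2.13 speaks of all data and does not name MRS. That 5-HT would be tested this way is a reasonable inference, no more.
- *The trial's main findings are at risk.* 5-HT by MRS is one readout among several scales, resting-state measures, serum markers and metabolomics. Nothing makes it primary, and neither the sample size in section 2.2 nor any clinical scale depends on it.

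A reader might also infer that GABA is sound once 5-HT is removed. It is not established as sound: its difficulty at 3T without editing is overlap rather than absence of signal, and the conflicts in the settings apply to it too.

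**Conclusion.** The point holds in conditional form. Assuming brain 5-HT of 0.0001 to 0.01 mM and an in-vivo detection limit of 0.1 to 1 mM, the planned acquisition falls short by about 10-fold at best and 10,000-fold at worst. Extra averaging is not a practical remedy even at the best corner. A reported hypothalamic 5-HT value would then be noise or an overlapping metabolite, and a difference in it could be misreported as a central serotonin effect of massage. Serum 5-HT and the clinical outcomes are untouched. The conflict between the sequence label and the stated method and echo time is visible in the article itself and needs no assumption about tissue levels.

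**What to change.** - Remove 5-HT from the MRS outcomes in the Abstract and section 2.11.3, unless validation evidence shows that this acquisition detects it in vivo.
- State that, without such evidence, the trial has no measure of brain 5-HT, and limit 5-HT conclusions to serum.
- Reconcile the sequence label in section 2.11.3 with STEAM at TE 30 ms, and state whether the acquisition is single-voxel or spectroscopic imaging.
- Quantify GABA from the stored spectral data rather than from a ppm position and a .jpg.

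Removing 5-HT changes wording only and adds no scan or patient. Reconciling the settings and keeping the spectral data is a small technical task. The downside is one mechanistic readout fewer.

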#### ^1^HNMR test

2.11.4

The blood samples will be obtained from an empty stomach in the morning before the beginning of admission treatment in the healthy group and the patient group, and on the following morning after the end of treatment. Before blood collection, the patient will be required to rest for 30 minutes, venous blood will be extracted, the serum will be centrifuged and stored in a refrigerator at –80 °C. Thereafter, before the detection, the serum samples will be resuscitated at the room temperature, and 400 L samples will be extracted and placed in a centrifuge tube with 30 L phosphate buffer (K2HPO4/NaH2PO4, 1.5 mol/L, pH = 7.4). Then, 170 L heavy water will be added and mixed. The serum samples will be centrifuged at 12,000r/min at 4 °C for 10 minutes, and 500 L supernatant will be taken and placed in a 5 mm NMR tube. The various common metabolites, differential metabolites, potential metabolic biomarkers, and metabolic pathways will be analyzed among each group. Superconducting NUCLEAR magnetic resonance spectrometer will be used for the data collection, and MestReNova-12.0.3-21384 software will be used for original data processing. Principal component analysis and orthogonal partial least squares analysis in multivariate statistical analysis will be performed using SIMCA-P14.0 software. MetabaAnlyst4.0 database will be employed and online metabolic data, http://www.metaboanalyst.ca, will be used to complete the metabolic pathway analysis.

#### ELISA detection

2.11.5

The estimation of the serum CRH, CRHR1, ACTH, COR, GABA, NE, PGE2, 5-HT levels will be carried out using enzyme linked immunosorbent assay (ELISA). The serum samples will be prepared and processed according to the instructions of each ELISA kit to calculate the OD value and to calculate the content using the curve formula.

### Quality control

2.12

The study quality management will be strictly carried out with reference to the Quality Management Standard for Drug Clinical Trials. The Massage therapy was in the charge of special personnel. A thorough training, practice, and assessment of the manipulation operation will be conducted before the start of the treatment to ensure that the time, intensity, and frequency of manipulation operations will be relatively consistent and will meet clinical standardization requirements as far as possible.

### Statistical method

2.13

Spss23.0 statistical software will be used for statistical analysis for all the data generated. Chi-square test will be used for enumeration data, paired *t* test will be used for the comparison of measurement data before and after the treatment. One-way analysis of variance (ANOVA) will be used for comparison between the treatment groups, with *P* < .05 as difference and *P* < .01 as significant difference.

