### Setting

2.2

The patients will be recruited from the Department of Zang-fu Massage, Affiliated Hospital of Changchun University of Chinese Medicine. Additionally, for participating in the trial, the patients will be screened strictly according to the diagnostic criteria, inclusion criteria, and exclusion criteria, and the requirements for the sample size estimation will be based on the clinical calculation formula employed for small sample size. The sample size (n = 16.76) will be calculated, that is, the therapeutic effect could be judged by the sample size of >16.67 people in each group. In this study, therefore 30 people will be observed in each group, which met the sample size estimation criteria.

The trial researcher will be able to record the subject's basic information (such as date of birth, sex) and answer patient trial screening questions. After the various patients have completed screening and enrolled, the trial study serial number, that is, the patient's unique identification number (SIN), will be obtained according to the enrollment time and order of enrollment, until the total number of observations (30 cases) was completed. Thirty healthy volunteers and 30 patients will be recruited for the study. After clinical evaluation and blood sampling, abdominal massage therapy will be adopted.

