#### Inclusion criteria for chronic insomnia (heart and spleen deficiency type)

2.6.1

The participants will have to meet the diagnostic criteria of chronic insomnia and the TCM symptoms of heart and spleen deficiency, and fulfill the following conditions: they will have to meet the diagnostic criteria for chronic insomnia, and meet the heart and spleen deficiency related symptoms of TCM. They must be between 50 and 55 years of age. They must not have been enrolled in any other clinical studies. They will have to sign informed consent and voluntarily participate in this research. Their Pittsburgh Sleep Index (PSQI) index score must be >7, the points of the Athens (AIS) scale score must be >6. The standard score of Depression Scale (SDS) and Anxiety Scale (SAS) must be ≤60. They must not experience work and life pressure during the observation period. They must not suffer from major cardiovascular and cerebrovascular diseases and other chronic diseases; their blood and urine analysis must be normal, as well as electrocardiogram, electroencephalogram, liver and kidney function test, blood sugar, and blood lipids and other inspection indicators must fall in the normal range. Patients with the above conditions lasting >1 year and frequency ≥3 times/wk will be included in this study.

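### Within-arm paired t tests stand beside a between-group ANOVA with no stated baseline adjustment, and the plan does not say which is the evidence of efficacy

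*Protocol article*

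**What the plan says.** The statistical method (section 2.13) names a chi-square test for counts and two tests for measurements. Within groups, a "paired *t* test will be used for the comparison of measurement data before and after the treatment". Between groups, "One-way analysis of variance (ANOVA) will be used for comparison between the treatment groups". The significance thresholds are worded as "with *P* < .05 as difference and *P* < .01 as significant difference". No baseline covariate is stated for the ANOVA, nor whether it is run on post-treatment values or on changes. Nothing ranks the two tests as evidence of efficacy.

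The abstract (Methods and design) sets the comparison: "Sixty insomnia volunteers will be randomly divided into a drug group and a massage group", while "30 healthy volunteers will be assigned to the healthy group". The only randomised contrast is therefore massage versus drug. Section 2.2 plans the numbers: "therefore 30 people will be observed in each group".

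Section 2.11.1 schedules the rating scales and heart rate variability (HRV) "before the first treatment, after the last treatment, and 4 weeks after the end of treatment (follow-up"), so a baseline value exists for each patient. Resting-state fMRI (2.11.2) and serum (2.11.4) are taken once before and once after treatment, and MRS (2.11.3) follows the fMRI session. Entry is selected on one of the outcome scales (2.6.1): "Their Pittsburgh Sleep Index (PSQI) index score must be >7".

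**The concern.** A before-after test in one arm measures everything that changed over the treatment period. Patients enter because their PSQI is high, so some fall in PSQI is expected without any treatment. Natural course, expectancy from a hands-on therapy without double blinding, and practice on a memory scale given three times can add to it. The paired test removes none of these.

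With two patient arms, the risk is a familiar one: one arm reaches significance, the other does not, and this is read as superiority. That pattern does not test the difference between the arms. Section 2.13 leaves the route open because it does not say that the within-arm tests are only descriptive.

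The between-group test does address the right question. However, it is stated without the baseline value, which is measured anyway and usually explains part of the outcome. Leaving it out widens the interval for massage versus drug in a trial with only 30 per arm.

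**Working it through.** **Inputs.** From the documents: 30 per arm (2.2) and P < .05 (2.13). Not in the documents: sidedness (two-sided .05 assumed), size of any non-specific improvement, effect size, SD and baseline-outcome correlation. These are assumed over ranges.

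**The plan's own figure.** Section 2.2 gives a required n of 16.76 per group (16.67 later in the same sentence) without effect size, SD or power, so it cannot be reproduced. As a two-sample, two-sided calculation with 80% power it would imply d = √(2 × 2.80² / 16.76) ≈ 0.97. As a paired calculation it would imply 2.80 / √16.76 ≈ 0.68. It therefore does not show which test the trial was sized for.

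**Step 1: paired tests when the arms do not differ.** Let both arms improve by the same dz (mean change divided by SD of change). The chance p that one arm's paired t test is significant comes from the noncentral t distribution with 29 df and noncentrality dz × √30. With independent arms, massage significant and drug not has probability p(1 − p); exactly one arm significant, in either direction, has probability 2p(1 − p).

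| dz | p | massage only, p(1 − p) | exactly one arm |
|---|---|---|---|
| 0.3 | 0.355 | 0.355 × 0.645 = 0.229 | 0.458 |
| 0.4 | 0.563 | 0.563 × 0.437 = 0.246 | 0.492 |
| 0.5 | 0.754 | 0.754 × 0.246 = 0.186 | 0.371 |

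The pattern that would wrongly favour massage is the third column, 19% to 25%. If the common improvement is instead set at 0.3 or 0.5 outcome SDs and the correlation varies from 0.3 to 0.7, the range is 7% to 25%.

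**Step 2: precision given up between arms.** ANCOVA multiplies the variance of post-treatment values by 1 − r². Thirty per arm with adjustment is then worth 30 / (1 − r²) without it, and the detectable d is multiplied by √(1 − r²). Unadjusted, the d detectable with 80% power at 30 per arm is 0.736.

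| r | 1 − r² | equivalent n per arm | detectable d |
|---|---|---|---|
| 0.3 | 0.91 | 30 / 0.91 ≈ 33 | 0.736 × 0.954 ≈ 0.70 |
| 0.5 | 0.75 | 30 / 0.75 = 40 | 0.736 × 0.866 ≈ 0.64 |
| 0.7 | 0.51 | 30 / 0.51 ≈ 59 | 0.736 × 0.714 ≈ 0.53 |

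In power (noncentral t, d = 0.5): 48% for post-treatment values alone, against 51%, 59% and 76% with ANCOVA at r = 0.3, 0.5 and 0.7. If the ANOVA uses change scores, the variance factor is 2 − 2r and power is 36%, 48% and 69%. ANCOVA is ahead of both at every correlation considered.

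**Step 3: which contrast the ANOVA tests.** If the healthy group is included, which the text leaves open, the overall F test can be significant only because patients differ from healthy people. With three groups of 30, identical patient arms and an assumed 1 SD gap to the healthy group, it is significant 98% of the time. This is a further reason to name the massage-versus-drug contrast.

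**The case against.** A reader might infer that efficacy is judged by the paired tests, so that natural improvement counts as efficacy. The documents do not say so. The sentence after the paired tests plans a between-group comparison, and the abstract frames the evaluation as massage against the drug and healthy groups. Sections 2.2, 2.3 and 2.10 do describe only massage for 30 patients, but that does not establish that the paired tests decide efficacy when the abstract randomises 60 patients to two arms.

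Nor is it right that no test uses baseline: a paired t test does. What is missing is a stated baseline adjustment between groups.

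The unadjusted comparison of randomised arms is valid, and its standard error already allows for chance imbalance. That stands: baseline adjustment is a gain in precision, not the correction of a bias. It can also be said that a condensed article leaves such detail to a fuller document. That has less force here, because section 2.13 makes affirmative choices of test and the change is a specific one.

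The three-visit point is limited too. It applies to the scales and HRV; fMRI, MRS and serum have two time points, and the scales can be compared visit by visit. The lack of a joint model is therefore not an error in itself.

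Finally, the gain may be small. At r = 0.3 it is worth about 3 extra patients per arm, and selecting patients on PSQI > 7 tends to lower the correlation, so r = 0.7 may be optimistic for PSQI.

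**Conclusion.** The point holds in a limited form. Section 2.13 places uncontrolled within-arm tests beside a valid between-group test without stated baseline adjustment, and does not say which one carries the efficacy conclusion.

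If the paired tests were read as efficacy evidence, equal arms would produce an apparent advantage for massage in about 19% to 25% of trials. This rests on an assumed common dz of 0.3 to 0.5, independent arms, 30 complete patients per arm and two-sided .05. The between-group test loses precision equivalent to about 3, 10 or 29 patients per arm at assumed correlations of 0.3, 0.5 or 0.7, compared with an adjusted analysis of the same data. None of these assumptions can be checked against the documents. The case for the change does not depend on their exact values, because it costs almost nothing.

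**What to change.** State in section 2.13 that efficacy is judged by the randomised massage-versus-drug contrast, adjusted for the baseline value of the outcome:

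- **Rating scales and HRV:** ANCOVA at the post-treatment visit and at the 4-week visit, or one mixed model over both visits with baseline, arm, visit and arm-by-visit.
- **Serum, MRS and other measures with two time points:** ANCOVA on the post-treatment value.
- **Within-arm changes:** keep them as descriptive summaries, with an explicit statement that they are not evidence of efficacy.
- **Healthy group:** report comparisons with it separately from the efficacy contrast.

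The cost is analysis wording only. The baseline values are already scheduled, the patient numbers do not change, and the SPSS software named in the plan fits both models.
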